#### 7.4.1 Specific criteria for withdrawal

No specific criteria.

#### 7.5 Replacement of individual subjects after withdrawal

After withdrawal, subjects from the transplant group will not be replaced. In the intended number of participants, there is allowed for some withdrawal.

If subjects from the 3 dialysis groups drop out within 18 months from inclusion because of renal transplantation, they are asked to participate in the transplant group, under the following conditions:

- \* only calcification scores will be measured with MSCT, in order not to exceed the radiation exposure
- \* if subjects are transplanted within 6 months after inclusion, they will be switched to the transplant group without extra investigations
- \* if subjects are transplanted after 6 months and before 18 months after inclusion, patients are asked to participate again in the study, in the transplant group.
- \* a new informed consent must be obtained.

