### 3. STUDY DESIGN

The study is a prospective cohort study, with a duration of follow-up of 3 years. The design is schematically depicted in the following flow charts.

[figure not shown]

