#### Treatment with renal transplantation

Patients in this group are included in the study at the moment of renal transplantation, with a living or cadaveric renal transplant. Immunosuppressive medication is given according to the conventional standard regimens, and is adjusted as required by clinical events.

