#### **7.4 Withdrawal of individual subjects**

Subjects can leave the study at any time for any reason if they wish to do so without any consequences. The investigator can decide to withdraw a subject from the study for urgent medical reasons.

Patients in the dialysis groups (nocturnal hemodialysis, conventional hemodialysis, peritoneal dialysis) that receive a renal transplant during the study period are asked to undergo a MSCT, pulse wave velocity measurement and laboratory investigation within one month after transplantation. This enables us to assess the primary and secondary endpoint, albeit after a shorter period of time than intended.

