#### 7.6 Follow-up of patients withdrawn from treatment

After withdrawal, follow-up is performed according to the study protocol as far as possible, as depicted in the following diagram, with different examples:

[figure not shown]

Example 1: when a patient treated with conventional hemodialysis receives a renal transplant after 1 ½ years, for this patient the study will end at 1 ½ years. Now all measurements, including calcium score and coronary MSCT and PWV will be done at 1 ½ years after inclusion, and within one month after the renal transplant.

Example 2: when a patient who is treated with peritoneal dialysis develops claustrophobic symptoms, follow-up is completed according to the study protocol, except for the MSCT.

Example 3: when a patient who is treated with a renal transplant and renal function deteriorates to a GFR less than 30 ml/min, follow-up will be done as planned apart from the coronary MSCT, because contrast medium cannot be given.

Example 4: when a patient treated with conventional hemodialysis receives a renal transplant before 1 ½ years, the patient is asked to participate again in the study; new baseline measurements will be performed, but the coronary MSCT will not be done at inclusion, nor after 3 years. In this case the total radiation exposure will not exceed than the exposure in the original study (maximum of 11.3 mSv).

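### The protocol gives conflicting baseline rules for dialysis patients transplanted within 6 months, and lets patients transplanted at 6–18 months enter two cohorts with no within-patient term in the named regressions

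*Protocol*

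**What the plan says.** Four places in the protocol govern a dialysis patient who is transplanted during the study.

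- **Section 5.1, Treatment with renal transplantation:** "Patients in this group are included in the study at the moment of renal transplantation". Time zero for the transplant cohort is the transplant.
- **Section 7.4:** dialysis patients transplanted during the study period "are asked to undergo a MSCT, pulse wave velocity measurement and laboratory investigation within one month after transplantation". No early period is exempt. The stated purpose is to save the endpoint of the dialysis record: "This enables us to assess the primary and secondary endpoint, albeit after a shorter period of time than intended".
- **Section 7.5:** for early transplants, "if subjects are transplanted within 6 months after inclusion, they will be switched to the transplant group without extra investigations". For transplants after 6 and before 18 months, "patients are asked to participate again in the study, in the transplant group".
- **Section 7.6, Example 4:** for a transplant at any time before 1½ years, "new baseline measurements will be performed, but the coronary MSCT will not be done at inclusion, nor after 3 years". There is no split at 6 months.

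Follow-up is fixed in Section 3: "The study is a prospective cohort study, with a duration of follow-up of 3 years". On analysis, Section 4.4 names linear regression on transformed scores. Section 9 names multinomial logistic regression for progression, regression for the group comparison, and univariate and multivariate linear regression corrected for the initial score. None of these mentions a patient who appears in more than one group or records of unequal length.

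**The concern.** Two separate problems arise, in different patients.

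**Transplant before 6 months.** These patients move to the transplant group and are not counted twice. If no scan is made at transplantation, the only available baseline is the scan from inclusion on dialysis, and progression on dialysis is then booked to transplantation. If dialysis progression is faster, as the protocol hypothesises for conventional dialysis, the primary contrast shrinks toward zero. An analysis plan written later cannot recover a scan that was never taken, so this has to be settled in the protocol.

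**Transplant at 6–18 months.** These patients get a new baseline, so nothing is carried over. However, 7.4 keeps their dialysis period as an endpoint and 7.5 enrols them again, so one person can supply a change score to a dialysis cohort and another to the transplant cohort. If a regression ignores this, its standard errors may be wrong, both for the modality comparison and for the risk-factor associations in the secondary objectives. Overlap is foreseeable: Section 4.1 recruits hemodialysis and peritoneal dialysis patients who are or could be eligible for the transplant waiting list, and Section 4.4 names transplantation among the reasons for dropout.

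**Working it through.** **1. The plan's own sample size.** Section 4.4 gives a mean of 2370, an SD of 352, a detectable difference of 15%, two-sided alpha 0.05, power 0.90 and 22 per group. The difference is 0.15 × 2370 = 355.5. The usual formula gives 2 × [(1.96 + 1.28) × 352 / 355.5]² = 20.6, so 21; the t-based version gives 21.6, so 22. The figure reproduces with SD 352, not with the 3.52 printed in the formula legend. Power at 22 per group is Φ(355.5 / (352 × √(2/22)) − 1.96) = Φ(3.350 − 1.96) = 0.918.

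**2. The rules side by side, transplant before 6 months.**

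| Section | New scan at transplantation? |
|---|---|
| 5.1 | Implied, since inclusion is at transplantation |
| 7.4 | Yes, within one month |
| 7.5 | No extra investigations |
| 7.6, Example 4 | Yes, new baseline |

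**3. Carry-over if 7.5 governs.** Assume progression linear in time, at yearly rate r_d on dialysis and r_t after transplantation. A patient transplanted at month 6 shows 0.5 r_d + 2.5 r_t instead of 3 r_t. The excess is 0.5 (r_d − r_t), which is 0.5/3 = 6/36 = 16.7% of the three-year contrast 3 (r_d − r_t). If a share f of the transplant group was switched at month 6, the contrast kept is 1 − f × 6/36. Power is recomputed as in step 1 with 355.5 multiplied by that factor.

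| f (assumed) | Contrast kept | Power, 22 per group |
|---|---|---|
| 0 | 100% | 0.918 |
| 10% | 98.3% | 0.909 |
| 25% | 95.8% | 0.894 |
| 50% | 91.7% | 0.867 |
| 100% (bound) | 83.3% | 0.797 |

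With an average of 3 months carried over and f = 25%, 97.9% is kept and power is 0.907. The power figures only set a scale, because the mean and SD in Section 4.4 describe the score, not its change.

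**4. Overlap, transplant at 6–18 months.** Let q be the share of a group that also appears in another and ρ the correlation between a patient's two records; neither is in the protocol. Assume equal group sizes and variances.

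- *Transplant minus one dialysis group holding all the re-entrants:* true variance over naive variance is 1 − qρ. For q = 0.1 to 0.5 and ρ = 0.3 to 0.8 this runs from 0.97 to 0.60. The true alpha, 2[1 − Φ(1.96/√ratio)], runs from 0.047 to 0.011, which is conservative.
- *Re-entrants spread evenly over the three dialysis groups:* the ratio is 1 − qρ/3 for each pairwise contrast and 1 − qρ/2 against the three pooled. At q = 0.25 and ρ = 0.5, the naive standard error is 1/√0.875 = 1.07 times the true one with a single comparator, but 1.02 and 1.03 with the even spread. At q = 0.4 and ρ = 0.7 the values are 1.18, 1.05 and 1.08.
- *Pooled risk-factor slope, trait the same in both records:* the ratio is 1 + qρ with two groups, from 1.03 to 1.40, with true alpha 0.053 to 0.098. With all four groups it is 1 + qρ/2, from 1.015 to 1.20, with true alpha 0.052 to 0.074. Both are anti-conservative.

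**5. Is ρ positive?** Not necessarily. If one scan closes the dialysis record and opens the transplant record, its error enters the two changes with opposite signs. With scan-error SD e, between-patient SD of yearly progression s, correlation of the true rates c, and t years on dialysis:

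ρ = (3t·c·s² − e²) / √[(t²s² + 2e²)(9s² + 2e²)].

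Section 4.4 puts measurement variation below 10%; take e as 5% to 10% of 2370 and the rest as assumptions.

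- e = 237, s = 50, t = 0.5, c = 0.5: ρ = −54,294 / √(112,963 × 134,838) = −0.44.
- e = 118.5, s = 352, t = 1.5, c = 0.7: ρ = 376,255 / √(306,869 × 1,143,221) = +0.64.

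**6. Unequal length.** A re-entrant's dialysis record covers 6 to 18 of 36 months, i.e. 17% to 50% of the planned follow-up, so its raw change is not comparable with a three-year change.

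**The case against.** The strongest reply is that the carry-over may never happen. Section 7.5 does not say which scan is the baseline; if 7.4 or Example 4 governs, a scan exists at transplantation and the dilution is zero. That stands as a limit on the size. It does not remove the conflict, and using the inclusion scan is the natural reading of 7.5 taken alone.

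A reader might infer that the primary contrast is biased by 17%. The protocol does not support this: 16.7% is the ceiling for one patient transplanted exactly at month 6, and the group effect is that figure times an unknown share. Little dilution is expected from patients who come from nocturnal hemodialysis, for whom the protocol's hypothesis is progression close to that after transplantation.

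A reader might also infer that the plan treats a patient's two records as independent people. No passage says so. The inference rests on the models named and on silence; a patient term is commonly left to a statistical analysis plan, and one not shown here may include it.

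Finally, standard errors 7% or 18% too wide for transplant versus dialysis would require every re-entrant to come from one comparator of equal size. Step 4 shows smaller values under an even spread, and step 5 shows that even the sign is open. Under positive correlation the primary contrast is conservative, so false-positive risk arises only for the pooled risk-factor slopes.

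**Conclusion.** The concern holds in limited form. The firm part is the contradiction between Sections 5.1, 7.4, 7.5 and 7.6 (Example 4) on the baseline of patients transplanted within 6 months. If 7.5 is followed as written, the transplant–dialysis contrast is diluted by at most 1.7% to 8.3% for an assumed switched share of 10% to 50%. This assumes linear progression and switching at month 6. It is modest, but systematic and avoidable.

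The second part is that 7.4 and 7.5 together allow one patient to supply a change score to two cohorts, while the protocol's named regressions carry no within-patient term. Standard errors may be wrong as a result. Their size and direction depend on the overlap and the within-patient correlation, and the protocol gives neither.

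**What to change.** 1. Reconcile Sections 5.1, 7.4, 7.5 and 7.6 so that every transplant-group record starts from the calcium-score scan within one month after transplantation that 7.4 already requests, including for transplants before 6 months.
2. In Section 9, analyse change per unit of time within modality, with patient-clustered standard errors or a patient random effect. Modality as a time-varying exposure is one acceptable way to do this, not the only one.
3. Add a sensitivity analysis with one record per patient.
4. Report how many patients were switched or re-entered, so that the shares assumed above can be replaced by counts.

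The cost is one low-dose calcium-score scan for early switchers, already foreseen in 7.4, and an amendment notified to the ethics committee under Section 11.3. On the upper doses in Section 7.3, an early switcher with five calcium-score scans and one coronary scan would receive 5 × 1.2 + 4.1 = 10.1 mSv, below the 11.3 mSv maximum given in Example 4.

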#### 7.6 Follow-up of patients withdrawn from treatment

After withdrawal, follow-up is performed according to the study protocol as far as possible, as depicted in the following diagram, with different examples:

[figure not shown]

Example 1: when a patient treated with conventional hemodialysis receives a renal transplant after 1 ½ years, for this patient the study will end at 1 ½ years. Now all measurements, including calcium score and coronary MSCT and PWV will be done at 1 ½ years after inclusion, and within one month after the renal transplant.

Example 2: when a patient who is treated with peritoneal dialysis develops claustrophobic symptoms, follow-up is completed according to the study protocol, except for the MSCT.

Example 3: when a patient who is treated with a renal transplant and renal function deteriorates to a GFR less than 30 ml/min, follow-up will be done as planned apart from the coronary MSCT, because contrast medium cannot be given.

Example 4: when a patient treated with conventional hemodialysis receives a renal transplant before 1 ½ years, the patient is asked to participate again in the study; new baseline measurements will be performed, but the coronary MSCT will not be done at inclusion, nor after 3 years. In this case the total radiation exposure will not exceed than the exposure in the original study (maximum of 11.3 mSv).

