### **4.3 Exclusion criteria**

- life expectancy < 3 months
- claustrophobia
- treatment incompliance, i.e. non-adherence to dialysis regimens and drug use
- GFR < 30 ml/min (according to MDRD formula) in renal transplant patients
- pregnancy

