#### Multislice CT-scanning

Scanning with multi-slice CT is extremely fast. A calcium score scan and a coronary CT scan require less than 10 seconds of time (3 heartbeats). The scans will be performed on a MSCT-scanner with at least 64 detector rows (Brilliance-64, Philips Medical Systems, Best,

The Netherlands). In contrast to contrast-enhanced-CT scans of the heart with a considerable radiation dose, a calcium score multi-slice CT scan allows for a lower image quality and therefore a much lower radiation dose (depending on patient size and gender, radiation exposure will vary between 0.4 and 1.2 mSv, corresponding with less than half a year of natural background radiation). Even when the calcium score scan is combined with a coronary multislice CT-scan, total radiation dose is about 4-5 mSv, which is much less than the radiation dose of a diagnostic CT-scan of the abdomen (10-15 mSv). In some patients a very low dose of beta-blocker (5 mg metoprolol) will be given intravenously when the heart rate is above 60/min, in order to improve imaging of the heart during scanning. This will only be done in patients without contra-indications against beta blockade, which information has to be given to the radiologist by the nephrologist through written confirmation.

To enable assessment of coronary stenosis, the scan will be performed during contrast material injection (40-50 ml of low-osmolar contrast agent), but only in dialysis patients or in patients with adequate renal function (GFR according to MDRD formula  $\geq 45$  ml/min).

Protocol calcium score scan: prospectively triggered non-contrast CT, 128 x 0.625 mm collimation, step and shoot technique; reconstruction of 3 mm sections every 1.5 mm; 120 kVp at 50-75 mAs; radiation dose 0.8-1.2 mSv.

Protocol coronary multislice CT: prospectively triggered post-contrast CT, 128 x 0.625 collimation, step and shoot technique; reconstruction of 0.9 mm sections every 0.5 mm; 120 kVp at 150-250 mAs, depending on patient size (weight >60 kg); radiation dose 2.5-4.1 mSv; scanning during injection of 60 ml contrast material (300mg/ml iodine) at flow rate of 6 ml/s, followed by 50 ml normal saline at the same flow rate; short delay will be set to 7 s to ensure optimum contrast enhancement; scan is finished within 3 heart beats.

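### Section 7.6 does not carry through the contrast limit of 7.3 (MDRD GFR of at least 45 ml/min): Example 1 sets no GFR condition after a new transplant, and Example 3 names 30 ml/min

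*Protocol*

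**What the plan says.** **The general rule.** Protocol 7.3 (Multislice CT-scanning) describes the coronary scan as a contrast scan that is extra to medical care. Contrast is given "but only in dialysis patients or in patients with adequate renal function (GFR according to MDRD formula" at or above 45 ml/min). The first risk listed for contrast is nephrotoxicity.

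**Exit after a transplant.** Under 7.4, dialysis patients who receive a transplant "are asked to undergo a MSCT, pulse wave velocity measurement and laboratory investigation within one month after transplantation". The type of MSCT is not specified and no renal-function condition is given. Example 1 in 7.6 is specific, for a hemodialysis patient transplanted at 1½ years: "Now all measurements, including calcium score and coronary MSCT and PWV will be done at 1 ½ years after inclusion", and within one month of the transplant.

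**Loss of graft function.** Example 3 in 7.6 concerns a transplant patient whose "renal function deteriorates to a GFR less than 30 ml/min, follow-up will be done as planned apart from the coronary MSCT". The reason given is that contrast is then not possible.

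**Enrolment.** Section 4.3 excludes on "GFR < 30 ml/min (according to MDRD formula) in renal transplant patients", so transplant patients at 30-44 ml/min may take part.

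**Whether there is a follow-up coronary scan.** The Summary places a contrast scan at inclusion and at 3 years. Example 4 presupposes the later one when it says of a re-enrolled patient "but the coronary MSCT will not be done at inclusion, nor after 3 years". The investigations table in section 3 marks the coronary MSCT at inclusion only.

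**The concern.** Section 7.6 is where staff would look for what to do when a patient changes treatment or loses graft function. In Examples 2, 3 and 4 it says which scan is left out. Example 1 leaves nothing out, names the coronary scan as included, and places it in the first month after transplantation. Followed literally, it would expose a new graft to contrast whatever its function, in cases where 7.3 forbids it. Example 3 attaches the bar on contrast to a lower GFR than 7.3 does, so a reader of 7.6 alone could take 30 ml/min as the working limit.

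At stake is graft safety, for a scan that serves only the study and contributes only to a secondary endpoint (change in coronary stenosis). A lesser matter is consistency: if some patients are handled under 7.3 and others under 7.6, stenosis data after transplantation will be collected unevenly.

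**Working it through.** The point rests mainly on comparing text.

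**1. The instructions side by side**

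| Place | Who | Condition for contrast |
|---|---|---|
| 7.3 | every study coronary scan | on dialysis, or MDRD GFR ≥ 45 ml/min |
| 7.4 | dialysis patient just transplanted | none stated; type of MSCT not specified |
| 7.6 Example 1 | hemodialysis patient just transplanted | none stated; coronary scan named as included |
| 7.6 Example 3 | transplant patient with falling GFR | scan omitted below 30 ml/min |
| 4.3 | transplant patients at enrolment | no contrast rule; excluded below 30 ml/min |

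**2. Example 1 against 7.3.** A recipient with a working graft is no longer a dialysis patient, so under 7.3 the scan needs a GFR of at least 45 ml/min. Example 1 does not say so. Adding only a cross-reference to 7.3 would leave one case open. A recipient who is still dialysed because the new graft is not yet working could be counted as a dialysis patient, and 7.3 would then allow contrast at any graft function. That loophole lies in the wording of 7.3 itself. It can also reach the transplant cohort, which section 5.1 includes at the moment of transplantation and which the section 3 table schedules for a coronary scan at inclusion. The exclusion in 4.3 might remove some of those patients, but 4.3 does not say when the GFR is to be assessed, and it does not apply to Example 1 patients, who enrolled while on dialysis.

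**3. Example 3 against 7.3.** Every GFR below 30 is also below 45, so omitting the scan in Example 3 agrees with 7.3. The difficulty is the band between the limits: 45 − 30 = 15 ml/min, that is a GFR of 30-44. Section 7.3 bars contrast there, 4.3 lets such patients enrol, and Example 3 does not mention them. Nothing in the protocol reconciles the two numbers.

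**4. Does a follow-up coronary scan exist?** The Example 3 point needs one. The radiation figures give an indirect check. The scan protocols in 7.3 give 0.8-1.2 mSv for a calcium scan and, for a coronary scan, "radiation dose 2.5-4.1 mSv". Calcium scans are scheduled four times. Example 4 refers to "the exposure in the original study (maximum of 11.3 mSv").

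- One coronary scan: 4 × 0.8 + 2.5 = 5.7 to 4 × 1.2 + 4.1 = 8.9 mSv. This lies below 11.3.
- Two coronary scans: 4 × 0.8 + 2 × 2.5 = 8.2 to 4 × 1.2 + 2 × 4.1 = 13.0 mSv. This range contains 11.3.
- With the other calcium dose range in 7.3 (0.4-1.2 mSv), only the lower ends change: 4 × 0.4 + 2.5 = 4.1 and 4 × 0.4 + 2 × 2.5 = 6.6 mSv.
- With the combined figure in 7.3 (calcium plus coronary scan, at most about 5 mSv), one coronary scan gives 5 + 3 × 1.2 = 8.6 mSv, again below 11.3.

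The stated maximum therefore exceeds what one coronary scan can give and is compatible with two. It is not reproduced exactly, so this supports the Summary and Example 4 but does not settle the matter.

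**5. Number of patients.** It cannot be calculated. The loss allowance pools transplantation with other causes, and no GFR distribution is given. Transplants before 18 months are directed by 7.5 and Example 4 towards the transplant group without a further coronary scan, so Example 1 mainly concerns later ones.

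**The case against.** The strongest reply is that no rule is contradicted. Section 7.3 states a categorical limit within the CT procedure itself, and 7.6 opens by saying that follow-up keeps to the protocol to the extent feasible. An example that does not repeat a safety condition does not lift it. All research activities take place at one centre (4.1), which should know the limit. Example 3 is true as written, since a patient below 30 is also below 45, and its figure may simply echo 4.3. If the section 3 table governs, there is no follow-up coronary scan and the Example 3 point affects nobody. The protocol describes no recipient who is dialysed after transplantation. The diagram that accompanies the examples could not be read and might carry a condition.

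Much of this stands. A reader might infer that 7.6 authorises contrast in a new graft at any function, or that Example 3 permits it at 30-44 ml/min. The text supports neither: 7.3 continues to apply, and Example 3 does not say that contrast is withheld only below 30. The reply also shows that the wording on dialysis patients has to be repaired in 7.3, because a change to 7.6 alone would leave the transplant cohort at inclusion uncovered.

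It does not dispose of Example 1. There the contrast scan is named and directed without a condition, in a section whose other examples state their exceptions. That does not depend on whether the 3-year scan exists, because Example 1 calls for the scan itself.

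**Conclusion.** The concern holds as an inconsistency in safety instructions, and the protocol should be amended. Example 1 directs a contrast scan within a month of a new transplant without the GFR condition that 7.3 requires. Example 3 names a threshold 15 ml/min below that of 7.3 and leaves graft patients at 30-44 ml/min with mixed instructions. The Example 1 part stands whichever scan schedule is correct. The Example 3 part assumes a follow-up coronary scan, as the Summary and Example 4 indicate and the section 3 table does not.

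The risk is contained by the general rule in 7.3 and by the single research centre, and nothing shows that any patient would in fact be scanned against that rule. The number exposed cannot be derived. A reader might also suspect an effect on the main result; there is none, because the calcium score comes from the non-contrast scan.

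**What to change.** Three wording changes:

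- **7.3:** State that a contrast scan in anyone with a renal transplant requires an MDRD GFR of at least 45 ml/min, and that a recipient still dialysed while a new graft is not yet functioning does not count as a dialysis patient for this purpose. This also covers the transplant cohort at inclusion.
- **7.6, Example 1:** Make the coronary MSCT subject to that limit. Where it is not met, do only the non-contrast calcium score scan, with the other measurements as planned.
- **7.6, Example 3:** Replace 30 by 45 ml/min, so that one contrast threshold applies throughout. The enrolment limit of 30 ml/min in 4.3 can stay.

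No visit, blood draw or scan is added. The cost is a few coronary stenosis values, at inclusion in recipients whose graft is not yet working, at exit after transplantation, and in graft patients at 30-44 ml/min. Section 7.3 already withholds the scan from most of these patients.

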**Nature and extent of the burden and risks associated with participation, benefit and group relatedness:**

- The study is an observational study, not an intervention-study.
- Participation does not influence or change the nature of the treatment, i.e. the modality of renal replacement therapy;
- Participation is associated with limited physical examination, questionnaires and blood sampling;
- Blood sampling is performed in combination with regular blood sampling, and requires a maximum of 20 cc blood per visit extra, once a year;
- Multislice CT-scan is performed at inclusion, and after 1, 2 and 3 years; this scan takes < 1 minute of time and radiation exposure is less than with conventional abdominal CT-scan; at inclusion and after 3 years, multislice CT-scan with intravenous contrast is performed to examine potential coronary stenosis.
- Yearly measurements of pulse-wave velocity are done with ultrasound (non-invasive), which takes 30 minutes of time.

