### **Secondary objectives:**

1. To assess whether frequent nocturnal hemodialysis and renal transplantation are associated with less progression of coronary artery stenoses, in comparison with conventional 3-times/week hemodialysis and with peritoneal dialysis;
2. To assess the association of calcium-homeostasis, in particular calcium, phosphate, PTH, and relevant medication, with the progression of coronary arterial calcifications and stenoses;
3. To assess the association of markers of inflammation, in particular CRP, interleukin-6, interleukin-1, von Willebrand factor, fibrinogen, with the progression of coronary arterial calcifications and stenoses;
4. To assess the association of calcification-inhibitors, in particular fetuin A, osteoprotegerin and matrix-Gla protein, with the progression of coronary arterial calcifications and stenoses.
5. To assess possible interaction of the abovementioned risk factors and the treatment modalities mentioned in the primary objective.

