#### 7.1.2 Secondary study endpoints

The secondary endpoints of the study are:

- change in pulse wave velocity
- change in coronary artery stenosis
- association between calcium, phosphate, PTH and change in coronary artery calcification score
- association between high-sensitivity-CRP, interleukin-6, interleukin-1, von Willebrand factor, myeloperoxidase, and change in coronary artery calcification score
- association between fetuin A, osteoprotegerin and matrix-Gla protein, and change in coronary artery calcification score
- cardiovascular events and mortality, assessed by the local investigator and the principal investigator separately

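### Stenosis change in the transplant cohort can be observed only in first-entry, contrast-eligible patients, yet secondary objective 1 states an unrestricted comparison with dialysis

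*Protocol*

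**What the plan says.** **Objective and endpoint.** Secondary objective 1 (protocol, section 2) asks whether frequent nocturnal hemodialysis and transplantation are "associated with less progression of coronary artery stenoses, in comparison with conventional 3-times/week hemodialysis and with peritoneal dialysis". The matching endpoint in section 7.1.2 is "change in coronary artery stenosis". Neither is restricted to a subset of patients.

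**Scan schedule.** The Summary, under burden and risks, states: "at inclusion and after 3 years, multislice CT-scan with intravenous contrast is performed to examine potential coronary stenosis". The investigations table in section 3 marks the coronary MSCT at inclusion only.

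**Re-entry.** Section 7.5 invites dialysis patients who are transplanted within 18 months into the transplant group, on condition that "only calcification scores will be measured with MSCT, in order not to exceed the radiation exposure". Example 4 in section 7.6 repeats this: "the coronary MSCT will not be done at inclusion, nor after 3 years".

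**Contrast and graft function.** Section 7.3 allows contrast "but only in dialysis patients or in patients with adequate renal function", defined there as an MDRD GFR of at least 45 ml/min. Example 3 in section 7.6 drops the coronary MSCT when graft GFR falls below 30 ml/min. The only graft-function exclusion at entry (section 4.3) is "GFR < 30 ml/min (according to MDRD formula) in renal transplant patients".

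**Exit scans.** Section 7.4 asks every dialysis patient transplanted during the study for an MSCT within a month, so that the primary and secondary endpoint can still be assessed. It does not say whether the coronary scan is included. Example 1 includes it for a transplant at 1½ years.

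**The concern.** The rules that decide who gets a second contrast scan differ between the cohorts being compared. Dialysis patients may have contrast without regard to GFR; transplant patients may have it only while the graft functions well enough. Patients who re-enter after an early transplant are placed in the transplant cohort but get no coronary scan there.

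Graft function is an outcome of transplantation and is plausibly related to vascular disease through calcium and phosphate control, which is the mechanism that the protocol itself proposes. A smaller stenosis change in the scored transplant patients could then partly reflect which grafts were scanned. An analysis plan can state the subset analysed, but it cannot supply scans that the protocol rules out.

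**Working it through.** No sample-size figure bears on this point: the 22 completers per group in section 4.4 are sized on the calcification score. The check is a comparison of passages, one dose sum and one illustration of size.

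**1. Who in the transplant cohort can have two contrast scans?**

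- First entry, GFR at least 45 at both scans: yes, if the Summary's 3-year scan applies.
- First entry, GFR 30-44 at either scan: no under section 7.3; yes under Example 3. Unresolved.
- First entry, GFR falling below 30: no under both.
- Re-entered after a transplant before 18 months: no, under section 7.5 and Example 4.

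Under either limit, being scored depends on graft function.

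**2. Does the radiation figure fit this reading of re-entry?** Example 4 gives a maximum of 11.3 mSv. The upper doses in section 7.3 are 1.2 mSv per calcium-score scan and 4.1 mSv per coronary scan.

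- Six calcium scans and one coronary scan: 6 × 1.2 + 1 × 4.1 = 11.3 mSv. This equals the stated maximum.
- Six calcium scans and two coronary scans: 6 × 1.2 + 2 × 4.1 = 15.4 mSv.
- For reference, the Summary's schedule of four calcium and two coronary scans: 4 × 1.2 + 2 × 4.1 = 13.0 mSv.

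Six plus one fits a patient scanned at inclusion and 1 year on dialysis and then four more times after re-entry, with the single coronary scan made on dialysis. Such a patient has no stenosis change in the transplant cohort, and the figure leaves no room for a coronary scan on leaving the dialysis cohort. This supports the reading but does not prove it, because the protocol does not show how 11.3 was obtained.

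**3. Dialysis patients transplanted before 18 months.** Section 7.4 plans an exit MSCT for all of them, with the secondary endpoint as part of its purpose. Section 7.5 and Example 4 allow only calcium scoring for those who re-enter. A patient who declines re-entry is covered by section 7.4 but not clearly by section 7.5. Whether an exit coronary scan is made is therefore unclear.

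**4. Illustrative size.** Inputs are 40-55 patients per cohort and 25% loss (Summary, Study design). The share of losses that are early transplants who re-enter is assumed to be 10-25%, and re-entrants are assumed to count within the 40-55.

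- Cohorts of 40: losses 3 × 0.25 × 40 = 30. Re-entrants 0.10 × 30 = 3 to 0.25 × 30 = 7.5, which is 7.5% to 18.75% of 40.
- Cohorts of 55: losses 3 × 0.25 × 55 = 41.25. Re-entrants 0.10 × 41.25 = 4.1 to 0.25 × 41.25 = 10.3, again 7.5% to 18.75% of 55.

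Contrast-ineligible grafts come on top. The protocol gives no share; each 10% of the cohort would be 4 of 40 or 5.5 of 55.

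**The case against.** The calcium-only rule for re-entrants is an openly stated radiation trade-off. The endpoint is secondary, and the primary endpoint needs no contrast. Handling of missing outcomes is normally left to the analysis plan. Re-entrants are unscored because of a radiation rule and not because of poor graft function, so their number does not measure selection on graft function. All of this stands, and it limits the weight of the point. It does not remove the mismatch between an unrestricted objective and scan rules that the protocol itself fixes.

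Four stronger readings are tempting, and the documents do not support them.

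- *Dialysis patients who leave before 18 months cannot be scored.* Section 7.4 plans an exit MSCT for those transplanted, and section 7.6 continues follow-up after withdrawal as far as possible. The rules are unclear; they are not a general bar.
- *The dialysis side consists only of patients who stayed.* Example 1 gives a patient transplanted at 1½ years an exit coronary scan, so some leavers contribute a change over a shorter interval. That scan may follow the transplant, so the graft limit could apply there too.
- *Grafts at GFR 30-44 are definitely unscorable.* This holds under section 7.3 but not under Example 3.
- *More than 10% of the transplant cohort is lost through re-entry in every case.* This follows only if all patients beyond the 22 completers count as losses: 18-33 per dialysis cohort, 54-99 in three, hence 14-45% at the same assumed share. But 22 is a completer target, and the stated loss is 25%, at which the range starts at 7.5%.

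**Conclusion.** The point holds in limited form. In the transplant cohort, change in stenosis is observable only in first-entry patients who are contrast-eligible at both scans, so the transplant side of secondary objective 1 rests on a subset selected partly on graft function. The limit that defines the subset is contradictory, leaving GFR 30-44 unresolved, and the exit-scan rules for early transplants do not agree clearly.

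The size is not documented. The 7.5-19% for re-entrants rests on the stated 25% loss and an assumed re-entry share; the share of ineligible grafts is unknown. The direction and amount of any bias cannot be derived from the protocol.

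A related conflict should be settled at the same time: read literally, the investigations table gives no patient who completes follow-up a second coronary scan, against the Summary. A table broken in conversion could explain this.

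**What to change.** 1. Reconcile three sets of statements, with the choice left to the investigators: the contrast limits (section 7.3 against Example 3, and both against the entry criterion in section 4.3); the exit-scan rules for dialysis patients transplanted before 18 months (section 7.4 against section 7.5 and Example 4); and the coronary MSCT schedule (Summary against the section 3 table).
2. Restate secondary objective 1 and the stenosis endpoint so that any transplant result applies to first-entry patients who were contrast-eligible at both scans, and is not read as the effect of transplantation in the whole cohort.
3. Report change in calcification score in that scored subset beside the full transplant cohort. Calcium scoring needs no contrast, so this shows how selective the subset is from scans already planned.

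The cost is protocol and analysis wording, with no extra scans. The downside is a narrower stenosis conclusion for transplantation.
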